#### Safety measures

General check-up: Liver function and renal function will be examined to evaluate the effect of basic drug therapy.Special check-up: After knee joint treatment, wound healing should be observed, and routine blood examination of white blood cells will be performed to assess whether there is an infection.

The study will record and process any PDT-related adverse events or SAEs experienced by participants.

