## Methods

### Trial design

This is a single-center, randomized, double-blind, blank-controlled trial with 3 groups: the control group, the “PDT once” group, and the “PDT twice” group. The curative effect will be compared statistically across groups. There will be 126 participants in total, with 42 in each group. The trial will be conducted at the Rheumatology and Immunology Department at the Integrated Hospital of Traditional Chinese Medicine, Southern Medical University. Further details can be seen in the flowchart of the trial design in Fig. 1.

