### Groups and sample size

The necessary sample size was estimated to be 99 based on a preliminary trial with a small sample size. During the preliminary phase, eighteen participants were included and randomly divided into 3 groups of 6. According to the protocol, differences in UCSS between week 8 and the baseline value were detected. The mean ± standard deviation of UCSS reduction was obtained at week 8 and week 0 individually: 0.33±0.817, −0.80±0.837, −1.0±1.000. The standard deviation was 0.873, and PASS 11 software was used to estimate the sample size by means of the following formula:

$$ 1-\beta =1- probF\;\left[{F}_{1-a,G-1,N-G,}\;\left(G-1\right),N-G, NV/{\sigma}^2\right] $$

The significance level, *α*, was set to 0.05; the power of a test, 1 − *β*, was 0.80; the number of groups, *G*, was 3; *N* represents the sample size; *V* represents the variance of the group averages, $$ V=\Sigma \left({\left({\mu}_i-\overline{\mu}\right)}^2\right)/G $$; σ represents the standard deviation.

A total of 126 participants will be included to allow for 20% loss to follow-up. There will be 3 groups:
Control group: (*n*=42) These individuals will receive micro-arthroscopic surgical procedures twice (day 0 and 4th week), and 0.9% saline will be administered instead of PS.PDT once group: (*n*= 42) Participants will receive PDT on day 0, followed by 0.9% saline administration instead of PS in the 4th week.PDT twice group: (*n*=42) Individuals will receive PDT twice: once on day 0 and once in the 4th week.

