### Randomization and blinding

We will recruit participants from our hospital, clinic, and by referral from other hospitals. To participate, all candidates must sign an informed consent form before entering the screening period. After the baseline survey, all identified participants will be randomly assigned to the 3 groups as previously stated. The block randomization method will be used for 1:1:1 randomization to ensure a balanced distribution between 3 groups. The random numbers will be generated using SAS 9.12 software. On this basis, randomization will be conducted by a professional nurse at the hospital follow-up center.

The researchers responsible for evaluations, application of the treatment protocol, and statistical analysis will be blinded to the group allocation of participants. The participants will also be blinded to group allocation. All researchers and patients in this trial will be informed not to communicate regarding the details of the groups. There is no difference in the appearance of PS solution and saline, enabling the double blinding to be maintained. PS or saline will be prepared by the professional nurse at the follow-up center, according to the random grouping table. Participants will be unblinded at the termination of this trial.

If emergency unblinding is deemed necessary, for example, if there is a serious adverse event (SAE) such as instrument fracture in the articular cavity, tissue hematoma, infection, or structural damage, researchers should determine the relevance of the event based on the grouping information. Effective treatment will be administered to those participants.

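### Adverse events are filtered by attribution to PDT, and after emergency unblinding relevance is judged from allocation, so the between-arm safety comparison is incomplete and open to differential recording

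*Protocol article*

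**What the plan says.** Two separate sentences of the protocol article matter here.

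- **Recording (Safety measures).** "The study will record and process any PDT-related adverse events or SAEs experienced by participants". Nowhere does the article say that events are recorded whatever their cause.
- **Judging relevance (Randomization and blinding).** The paragraph begins "If emergency unblinding is deemed necessary, for example, if there is a serious adverse event (SAE" and gives instrument fracture, hematoma, infection and structural damage as examples. It then says that "researchers should determine the relevance of the event based on the grouping information". No other basis for judging causality is given.

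The context for both is as follows.

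- **Blinding.** Outside emergencies, "The researchers responsible for evaluations, application of the treatment protocol, and statistical analysis will be blinded to the group allocation of participants". Participants are blinded too.
- **Exposure of the control arm (Groups and sample size).** "These individuals will receive micro-arthroscopic surgical procedures twice (day 0 and 4th week), and 0.9% saline will be administered instead of PS". The two PDT arms also have an operation on day 0 and at week 4.
- **Unfiltered checks (Safety measures).** "Liver function and renal function will be examined to evaluate the effect of basic drug therapy". The wound and the white cell count are also checked after the knee procedure, to look for infection. Neither check is restricted by arm or by attribution.
- **Arm sizes (Trial design).** "There will be 126 participants in total, with 42 in each group".

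**The concern.** A sham-procedure control is valuable for safety because it shows what the operation does without the photosensitizer. That works only if events are captured the same way in every arm. A rule that asks whether an event is due to PDT before recording it puts a judgement ahead of the data. Staff who do not know the allocation have little to base that judgement on. Staff who do know it have an obvious reason to answer differently by arm.

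The Background says that the effectiveness of PDT in the clinical treatment of RA has not been reported and calls the trial a pilot study. The Background, Discussion and Strengths and limitations sections already describe its adverse effects as mild or fewer than those of alternatives. The control arm is what could test that description. Events that were never recorded may not be recoverable later.

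**Working it through.** The article states no adverse event rate and no safety calculation, so there is no figure to reproduce. The check sets the rules side by side and then uses assumed rates to show the range.

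**Step 1: which events does the filter reach?** The recording sentence can be read in two ways.

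- *The qualifier covers adverse events only.* All SAEs are recorded in every arm, and non-serious events are filtered.
- *The qualifier covers both.* SAEs are filtered as well.

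Non-serious events are filtered on either reading.

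**Step 2: blinded attribution.** Let the true event rate be *p* in each arm, and let blinded staff attribute a fraction *r* of events to PDT, the same in all arms. The recorded rate is *r* × *p* everywhere, so the recorded difference is 0. What is lost is (1 − *r*) × *p* per arm. For example, with assumed *p* = 0.10 and *r* = 0.5:

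- true events per arm: 42 × 0.10 = 4.2
- recorded per arm: 4.2 × 0.5 = 2.1
- recorded in the whole trial: 6.3 of 12.6

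A real difference of *d* between arms would shrink to *r* × *d*. The harm here is incompleteness, not a false PDT excess.

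**Step 3: attribution after the code is opened.** The listed emergencies can follow arthroscopy in any arm. In a control patient, who received no photosensitizer, such an event is unrelated to PDT almost by definition once allocation is known. In a PDT patient the identical event can be called related. If SAEs are filtered, this makes recording differ by arm. If all SAEs are recorded, it still makes the related/unrelated label on them differ by arm.

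**Step 4: how large could the gap in step 3 be?** Let *p* now be the rate, equal in all arms, of events judged with allocation known. Assume every such event is counted in the two PDT arms (2 × 42 = 84 patients) and a fraction *c* in the control arm (42 patients). The counted gap is *p* × (1 − *c*). The false-signal rate below is the chance that a two-sided Fisher exact test at 0.05 rejects, summed over both binomial distributions. The article plans no such test; it serves only as a yardstick. Each cell gives the gap in percentage points and then the false-signal rate.

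| *p* (assumed) | *c* = 0 | *c* = 0.25 | *c* = 0.5 | *c* = 1 |
|---|---|---|---|---|
| 0.10 | 10; 47% | 7.5; 19% | 5; 8% | 0; 3% |
| 0.20 | 20; 99% | 15; 61% | 10; 25% | 0; 4% |
| 0.30 | 30; 100% | 22.5; 85% | 15; 42% | 0; 4% |
| 0.40 | 40; 100% | 30; 96% | 20; 61% | 0; 4% |

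The *c* = 0 column is a worst case. The *c* = 1 column is what recording every event in every arm would give.

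**The case against.** The strongest reply is that two rules should not be merged into one. The allocation-based judgement is written for emergency unblinding, with an SAE as the example. Nothing ties it to the recording of ordinary adverse events, for which evaluators are blinded. This stands. A reader might infer that all relatedness is judged from allocation, so that the control arm would show almost no events by construction. The text does not support that: step 2 shows that blinded attribution at a common rate produces no false gap.

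Other parts of the reply:

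- **SAEs may not be filtered.** On one natural reading all are recorded, including the listed emergencies in control patients. This stands as a possibility, but the sentence does not settle it.
- **Other safety data are unfiltered.** Wound healing, white cells, and liver and renal function are checked without regard to attribution, and Evaluation procedure adds general condition and vital signs. So it would be too strong to say that safety cannot be compared without bias. These checks do not replace adverse event recording, however, and would not systematically capture hematoma, instrument fracture or structural damage.
- **A tally such as 8 of 84 against 0 of 42 is a worst case.** It needs an assumed 10% rate, every PDT-arm event counted and no control event counted, none of which the article prescribes. The upper 95% bound of 6.9% for 0 of 42 (1 − 0.05^(1/42)) reflects the arm size under any recording rule and is no evidence of this defect.
- **Bias in the UCSS is speculative.** A reader might infer that whoever opens the code later scores that patient's ultrasound. The article does not say so, and emergency unblinding would probably involve few patients. It does not rule it out either, so a safeguard is reasonable.
- **The stated aim is efficacy, and an article condenses.** No between-arm safety test is planned, and fuller definitions may sit in the full protocol. But the two sentences criticized are rules the article states, not details it omits.

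**Conclusion.** The point holds in limited form. As written, non-serious adverse events are recorded only if attributed to PDT, it is unclear whether SAEs are filtered too, and relevance is judged from allocation after emergency unblinding. Because all arms have arthroscopy twice, procedural events may be lost from every arm. For unblinded events, the same occurrence may be classed differently by arm. The between-arm safety comparison is therefore incomplete and open to differential recording. It is not shown to be biased in every respect.

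The size is unknown because the article gives no event rate and no frequency of unblinding. Under the assumptions of step 4, the false gap lies between zero and the full rate of the events judged with allocation known. If few codes are opened, the main loss is the under-recording in step 2. Nothing here bears on the sample size or on the primary analysis.

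**What to change.** 1. In Safety measures, state that all adverse events and SAEs in all three groups are recorded regardless of suspected cause and reported by arm as all-cause rates. This also removes the ambiguity about SAEs.
2. In Randomization and blinding, state that relatedness is assessed and documented before any code is opened, and remove allocation as the basis for causality in the sentence "researchers should determine the relevance of the event based on the grouping information". Emergency unblinding itself stays available.
3. State that any opened code is kept from the UCSS assessors.

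The cost is a few sentences and a CRF page for events of any cause. The small downside is that more events have to be recorded.

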### Data management and statistical analysis

#### Data management

The project administrator will develop strict procedures to ensure that the data are well preserved and traceable. During this trial, the raw data from participants and clinical assessments will be collected by data collectors on the CRFs created by the statistician. Furthermore, all of the data will be precisely entered into a password-protected computer within 2 weeks after data collection. After data collectors have entered all the data, the CRFs and signed informed consent forms will be handed over to the administrator for preservation.

The quality control personnel and inspector, as the designated representatives of the principal investigator, will have the right to supervise this trial and determine whether it is being carried out in accordance with the trial procedures. The CRFs will be filled out by the researcher, and the data will be recorded completely, accurately, clearly, and in a timely manner. The inspector shall check the CRFs in accordance with the original data. If there are any errors or omissions, the researcher will be asked to correct them in a timely manner and to sign and date the corrections in order to keep the original record in an easily accessible form. The CRFs will be handed over to the clinical trial data manager for data entry and management. For completed case report forms, there will be corresponding records and signatures by the researchers, inspectors and administrators. All these records will be properly preserved. To ensure confidentiality, the data disseminated to all project team members will be free of any information that identifies the participants.

The Department of Health Statistics of Southern Medical University will be responsible for data entry and modification. The data administrators need to check the CRFs again before entering the data. The researchers should answer any questions from the question request form (QRF) and return to the clinical inspector, who should properly preserve the document, as soon as possible. The data manager will record two copies of the data and verify that they are identical. During the data entry process, if errors are found in the entries, they should be registered and reported in a timely manner with the input of the leading researchers. A data range check and a logical check will be performed based on the ranges and interrelations of all index values in the CRF, and a corresponding computer program will be written to ensure that incorrect data cannot be entered. When a problem is found, QRFs can be issued again if necessary. After the data entry and verification have been completed as required, the original CRFs will be archived and stored in form number order and reviewed in the search catalog. The electronic data files include a database, checking procedures, analysis procedures, and analysis results, among other items. All original documents should be kept in accordance with Good Clinical Practice (GCP).

#### Data monitoring

The overall data quality will be monitored by the clinical research assistant of the Hospital GCP Center, which is independent of the sponsor and competing interests, throughout the study. The completeness and authenticity of the original data will be subject to checks at any time. After this trial is completed, all data will be kept for 15 years and then deleted.

#### Statistical analysis

SPSS 20.0 statistical software will be used to analyze the measurement data, described as the means ± standard deviations ($$ \overline{x}\pm s $$), and the main evaluation index (improvement in the UCSS compared with the baseline value) will be analyzed by single-factor variance analysis among the three groups. ANOVA will be used for repeated measurement data of the secondary evaluation indicators to explore the principal and interactive effects of grouping and time. Multiple paired *t*-tests comparing two time points (before and after treatment) will be used to analyze repeated measurements. Single-factor ANOVA will be used to compare the differences at the same time points after treatment between the three groups. Differences will be statistically significant at *P* <0.05.

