### Outcome and safety measures

#### Outcome measures

Primary outcome measure

The Ultrasound Compound Score of Synovitis (UCSS) will be calculated according to the EULAR-OMERACT combined scoring system for grading synovitis in rheumatoid arthritis [11]. Improvement in the UCSS compared with the control group will be the primary endpoint.
(2)Secondary outcome measures
Clinical evaluation of knee joints: The circumference will be measured 2 cm above the upper edge of the patella, and joint flexion and extension will be measured to assess the range of motion.DAS28-ESR: DAS28-ESR= 0.56 × the total number of tender joints + 0.28 × the total number of swollen joints + 0.70 × ln(ESR) + 0.014 × general health assessment score.Antibody levels: Serum will be collected by centrifugation, and then the RF and anti-CCP antibodies will be detected by a standard commercially available test kit.Inflammation indicators: Serum will be obtained by centrifugation, and then ESR and CRP will be detected by standard commercially available test kits.X-ray: X-rays of the knee joint will be used to evaluate bone destruction.Pathological biopsies of synovial tissue: The synovium of the joint, which will be acquired before laser irradiation during each operation, will be fixed, embedded by dehydration, and sectioned. The synovium will be stained with hematoxylin and eosin for histological evaluation, and synovial histopathology will be observed, including synovial cell proliferation, inflammatory cell infiltration, and angiogenesis (pannus formation). The pathological biopsy of synovial tissue will strictly follow the clinical diagnostic protocol. The research nurses will collect specimens with special specimen boxes, record basic information on the subjects, and then send specimens to the pathology department for testing and preservation as soon as possible.

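### One mean ± SD and ANOVA rule covers ESR, CRP, RF and anti-CCP with no allowance for skew and no baseline covariate; if these markers are right-skewed, power is lost

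*Protocol article*

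**What the plan says.** The Statistical analysis section of the protocol article states one approach for quantitative outcomes. SPSS "will be used to analyze the measurement data, described as the means ± standard deviations". For the secondary outcomes, "ANOVA will be used for repeated measurement data of the secondary evaluation indicators", to examine group, time and their interaction. Within arms, "Multiple paired *t*-tests comparing two time points (before and after treatment) will be used to analyze repeated measurements". Between arms, "Single-factor ANOVA will be used to compare the differences at the same time points after treatment between the three groups". The threshold is common to all: "Differences will be statistically significant at *P* <0.05".

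The Outcome measures section places four laboratory markers under this approach: "the RF and anti-CCP antibodies will be detected by a standard commercially available test kit", and "ESR and CRP will be detected by standard commercially available test kits". Table 2 schedules antibody levels and inflammation indicators at baseline and at weeks 4, 8, 24 and 48, so every patient should have a baseline value.

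No transformation, rank method or distribution check is named for any outcome, and no baseline covariate is named for any comparison between arms.

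**The concern.** Serum concentrations and sedimentation rates cannot be negative and may have a long upper tail. If they do, the mean and SD describe a typical patient poorly, and a few large values supply much of the within-group variance in an ANOVA on the raw values. The F-test then has a swollen denominator and misses effects that it could have shown.

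Two features of the protocol make the question fair. Its DAS28 formula enters ESR as a natural logarithm, while ESR as an outcome in its own right falls under the blanket mean ± SD rule. And the rheumatoid factor criterion is only one of seven, of which any four suffice, so patients with and without rheumatoid factor can both enter.

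The comparison of arms at each visit is also unadjusted. The paired t-tests use baseline, but only within an arm. The repeated-measures ANOVA may carry baseline as a time level, but not as a covariate. If baseline predicts follow-up, precision is given away.

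At stake are the comparisons of four secondary markers, not the primary result.

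**Working it through.** **Reference figure.** The plan states no power, SD or expected effect for these four markers, so there is no figure of its own to reproduce. The calculation below is illustrative.

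**Inputs from the protocol.**
- Three arms, 1:1:1; one-way ANOVA; two-sided reading of P < 0.05.
- Evaluable total 99, so 99 / 3 = 33 per arm. Allowing for 20% loss, 33 / 0.8 = 41.25, rounded up to 42 per arm, or 126 in all.

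**Assumptions, not in the protocol.**
- Lognormal follow-up values, with log-scale SD σ from 0.3 to 1.5.
- Both PDT arms at the same ratio r to control; r = 0.6 in the main case.

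**Log scale.** The protocol's own power formula applies, with noncentrality λ = N·V/σ². For group means 0, ln r, ln r, V = (2/9)(ln r)². With r = 0.6, ln r = −0.511 and V = 0.0580, so λ = 99 × 0.0580 / σ² = 5.74 / σ². This gives λ = 23.0, 8.97, 5.74 and 3.99 at σ = 0.5, 0.8, 1.0 and 1.2. The noncentral F distribution on 2 and 96 degrees of freedom then gives power of 99%, 76%, 55% and 40%.

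**Raw scale.** There is no simple formula, so trials were simulated and the same F-test was applied to the untransformed values.

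| log-scale SD | raw power | log power |
|---|---|---|
| 0.5 | about 98% | about 99% |
| 0.8 | about 65% | about 76% |
| 1.0 | about 40% | about 55% |
| 1.2 | about 25% | about 40% |

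**Same comparison at a fixed benchmark.** With 42 per arm, and r chosen at each SD so that log-scale power is 80%, raw-scale power is 79% (SD 0.3), 76% (0.5), 69% (0.8), 63% (1.0), 56% (1.2) and 44% (1.5).

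**False positives.** With no effect and 33 per arm, the simulated rejection rate on the raw scale is 0.050 at SD 0.5, 0.043 at 0.8, 0.039 at 1.0 and 0.035 at 1.2. The test is at or below its nominal level.

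**Weight of extreme values.** With 42 per arm, the two most extreme values in an arm carry on average 38% of the within-group sum of squares at SD 0.5, 50% at 0.8 and 57% at 1.0.

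**Baseline.** Assume a correlation of 0.7 between log baseline and log follow-up, r = 0.7, SD 0.8 and 33 per arm. Power is 36% on raw values, 44% on log values, and 74% on log values with log baseline as covariate.

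**Counter-case.** For near-normal data (mean 50, SD 15) with a shift of −10 in both PDT arms and 42 per arm, raw power is about 89% and log power about 81%.

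**The case against.** The strongest objection is that the protocol names families of tests and never says that values stay untransformed. ANOVA on logarithms is still ANOVA, and transformations and assay-limit rules are commonly settled in an analysis plan, which is not shown here. This stands in part. A reader might infer that the raw scale is mandated; it is only the plain reading. But the mean ± SD summary is explicit, and a method is stated for these outcomes, so the point is about a stated choice and not only about missing detail.

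Second, the protocol gives no distribution for any of the four markers. The logarithm in DAS28 concerns ESR alone and is part of a fixed index, not a choice of analysis scale. This stands: skew is an assumption throughout.

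Third, the size depends on the effect as well as the spread. PDT is delivered inside one joint, and all arms receive systemic drugs, so a 40% fall in serum markers may be generous. At a ratio of 0.8 and log-scale SD 0.8, power is about 15% on raw values and 19% on log values; at 0.9 it is about 7% and 8%. Changing the scale alone does not rescue such comparisons.

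Fourth, a reader might infer that a few high values could produce a spurious positive result. The simulations show the opposite: the raw test becomes conservative.

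Fifth, a reader might think that the log scale is free. It needs no extra patients, but it changes what is estimated, and it loses about 7 to 8 points of power in the counter-case above.

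**Conclusion.** The point holds as a minor, conditional one. The protocol applies mean ± SD, paired t-tests and ANOVA without a baseline covariate to ESR, CRP, RF and anti-CCP, with no allowance for skew. If the markers are right-skewed with a log-scale SD of about 0.8 or more, a single-visit comparison at a ratio of 0.6 and 33 per arm loses about 11 to 15 points of power. At 0.5 or less the loss in that comparison is negligible. Leaving out the baseline covariate can cost more than the choice of scale: 30 points in the example, 74% against 44% on the log scale, under an assumed correlation of 0.7.

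The documents do not support saying that these markers are known to be skewed, that raw values are required, or that the planned tests would give too many false positives. The primary UCSS analysis and the sample size are unaffected.

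**What to change.** Add a sentence or two to the Statistical analysis section, before any unblinded data are seen, for these four markers only:

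- Analyse ESR, CRP, RF and anti-CCP after log transformation, with the log baseline value as covariate in comparisons between arms.
- Report geometric mean ratios with 95% confidence intervals.
- Summarise by median and quartiles in place of mean ± SD.
- State a rule for values below and above the assay limits, for example half the lower limit for values below it.

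No extra patients, visits or measurements are needed, because Table 2 already schedules the baseline values. The costs are that results become ratios instead of differences, that the assay-limit rule is somewhat arbitrary (results for any marker with many values at a limit should be checked against another constant), and that a little power is lost if a marker proves near-normal with an additive effect. Fixing the scale in advance also avoids choosing it after the results are known.

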#### The inclusion and exclusion criteria

The inclusion and exclusion criteria for the patients are presented in Table 1.

**Table 1 Tab1:** Inclusion and exclusion criteria

*Inclusion criteria*	
*1. Male or female patients aged between 18 and 70 years* *2. Patients who meet the diagnostic criteria for RRA* *3. Patients with swelling of at least one knee for 1 month* *4. Patients with synovial hyperplasia confirmed by ultrasound or MRI: UCSS ≥ 2 points and/or single-site MR scores ≥2 points* *5. Patients who are capable of signing informed consent and completing the trial as required* *6. Patients who have good compliance and will complete follow-up*	
*Exclusion criteria*	
*1. Patients with severe primary diseases, such as disorders of the cardiovascular system, liver, kidneys, brain, or hematopoietic system* *2. Patients with infections or coagulation abnormalities* *3. Breastfeeding or pregnant women* *4. Patients who are allergic to anesthetics or PSs* *5. Patients who have undergone intra-articular drugs injection within the past month* *6. Patients with arthritic knee joints that show osteotropic ankylosis on X-ray examination*	

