### Evaluation procedure

The researchers will record participants’ postoperative improvement and general condition, including body temperature and respiration, pulse, and heart rate, during face-to-face follow-up visits. The items evaluated during each follow-up visit are shown in Table 2. All the data will be uploaded to the case report form (CRF) by rigorously trained data collectors. To reduce the rate of loss to follow-up, we will also communicate with participants by a variety of methods, including WeChat, telephone, text message, and e-mail, to remind them to return for further examination.

**Table 2 Tab2:** Follow-up plan

***Follow-up time***	***Evaluation index***
*Baseline*	*UCSS, clinical evaluation of knee joints, DAS28, antibody levels, inflammation indicators, X-ray, routine blood test, routine urine test, blood biochemical test, infectious disease screening*
*W0* *(first operation)*	*Pathological biopsies of synovial tissue*
*W4±3 d* *(second operation)*	*UCSS, clinical evaluation of knee joints, DAS28, antibody levels, inflammation indicators, pathological biopsies of synovial tissue*
*W8±3 d*	*UCSS, clinical evaluation of knee joints, DAS28, antibody levels, inflammation indicators, blood biochemical test*
*W24±5 d*	*UCSS, clinical evaluation of knee joints, DAS28, antibody levels, inflammation indicators*
*W48±5 d*	*UCSS, clinical evaluation of knee joints, DAS28, antibody levels, inflammation indicators, X-ray*

*W* week, *d* days

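### The primary UCSS analysis is a valid but unadjusted one-way ANOVA on change; adding baseline UCSS as a covariate would usually make it more precise at the cost of one degree of freedom

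*Protocol article*

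**What the plan says.** The Statistical analysis section names the primary test: "the main evaluation index (improvement in the UCSS compared with the baseline value) will be analyzed by single-factor variance analysis". A single-factor model contains treatment arm and nothing else. The Groups and sample size section uses the same unadjusted F test, so the plan is consistent with itself here.

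Baseline UCSS will be available for everyone. The baseline row of Table 2 (Evaluation procedure) begins "UCSS, clinical evaluation of knee joints, DAS28, antibody levels, inflammation indicators, X-ray, routine blood test". Randomization and blinding describes blocked 1:1:1 allocation and mentions no stratification by UCSS. Nothing else in the article adjusts for baseline UCSS, in the design or in the analysis.

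The entry criterion that bears on baseline is "UCSS ≥ 2 points and/or single-site MR scores ≥2 points" (Table 1).

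**The concern.** Subtracting the baseline value is not the same as adjusting for it. A change score fixes the baseline coefficient at 1. If baseline and follow-up are imperfectly correlated and have similar spread, change is negatively correlated with baseline, so an arm that happens to start higher tends to show a larger fall whatever the treatment does. With 42 randomized and 33 evaluable per arm, and no stratification by UCSS stated, some chance difference between arms must be expected. ANCOVA estimates the coefficient from the data and removes that part of the error.

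What is at stake is precision: wider confidence intervals than the collected data allow and, if the true effect is modest, lower power.

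**Working it through.** **Inputs from Groups and sample size.** Pilot means ± SD of the week-8 change are "0.33±0.817, −0.80±0.837, −1.0±1.000", read here in the order control, PDT once, PDT twice. "The standard deviation was 0.873". Alpha is 0.05, power 0.80, with three groups. Evaluable N is 99 (33 per group), and 126 after 20% loss.

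**Assumed.** The correlation rho between baseline and follow-up UCSS, and the ratio k = SD_baseline / SD_follow-up. The document gives neither.

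**Step 1: the plan's own figure.** The protocol's formula is noncentral F power with λ = N·V/σ² and V = Σ(μ_i − mean)²/3.
- Means as printed (+0.33, −0.80, −1.0): the mean is −0.49 and V = (0.82² + 0.31² + 0.51²)/3 = 0.343. Then V/σ² = 0.343/0.762 = 0.450. Nine per group suffice (N = 27, power 84.2%), not 99. At 33 per group power exceeds 99.9%.
- First mean −0.33: the mean is −0.71 and V = (0.38² + 0.09² + 0.29²)/3 = 0.0789. Then V/σ² = 0.1035. The smallest design is 33 per group, N = 99, power 81.2%. This reproduces the stated figure.
- Loss: 33/0.8 = 41.25, so 42 per group and 126 in total. This also reproduces.

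**Step 2: variance ratio, ANCOVA to change score.** Var(change) = s_F² + s_B² − 2·rho·s_F·s_B and Var(ANCOVA) = s_F²(1 − rho²). The difference is (s_B − rho·s_F)², which is never negative but is zero when k = rho. The ratio is (1 − rho²)/(1 + k² − 2·rho·k). With k = 1 it reduces to (1 + rho)/2.

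| rho | k = 1 | k = 0.7 | k = 0.5 |
|---|---|---|---|
| 0.3 | 0.65 | 0.85 | 0.96 |
| 0.5 | 0.75 | 0.95 | 1.00 |
| 0.7 | 0.85 | 1.00 | 0.93 |

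**Step 3: omnibus power at 33 per arm**, with the inputs that reproduce 99, k = 1 and one degree of freedom spent on the covariate.

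| Analysis | λ | Power | N for 80% |
|---|---|---|---|
| Change-score ANOVA | 99 × 0.1035 = 10.2 | 81.2% | 99 |
| ANCOVA, rho 0.3 | 10.2/0.65 = 15.8 | 94.8% | 66 |
| ANCOVA, rho 0.5 | 10.2/0.75 = 13.7 | 91.3% | 75 |
| ANCOVA, rho 0.7 | 10.2/0.85 = 12.1 | 87.4% | 84 |

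**Step 4: confidence interval for one arm against control**, which does not depend on the sign of the first pilot mean. The unadjusted 95% half-width is about 1.96 × 0.873 × √(2/33) = 0.42. Multiplying by √0.65, √0.75 and √0.85 gives 0.34, 0.36 and 0.39, which is 19%, 13% and 8% narrower. These figures again take k = 1.

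**Step 5: error from a chance imbalance.** With k = 1, a baseline difference d shifts the unadjusted contrast by −(1 − rho)·d. At rho = 0.5 the baseline SD implied by an SD of change of 0.873 is also 0.873. A one-standard-error imbalance is 0.873 × √(2/33) = 0.215, and it shifts the contrast by 0.5 × 0.215 = 0.11 UCSS points.

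**Step 6: is the planned analysis biased?** In a simulation with no treatment effect (33 per group, 4,000 runs, rho from 0.2 to 0.8), the average error of both analyses was within 0.005 SD of zero. The standard errors were 0.310 (change score) against 0.244 (ANCOVA) at rho 0.2, and 0.159 against 0.151 at rho 0.8.

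**The case against.** The strongest defence is that nothing here is wrong. Under randomization the change-score ANOVA is unbiased and has valid type I error, and its standard error already allows for chance imbalance. The trial is sized on the same test, and an analysis plan that is not shown might add the covariate. All of this stands except the last point, which carries less weight: the protocol does not leave the model open but names one with a single factor.

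The size of the gain is also open to challenge. The ratio (1 + rho)/2 needs equal variances. The UCSS route into the trial is a lower threshold, which may make the baseline SD smaller than the follow-up SD, and the gain can then shrink to nothing (Step 2). That stands too.

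A reader might infer more than the document supports:
- **That the unadjusted result would be biased.** It would not. Chance imbalance gives conditional error in a particular trial, not bias over randomizations.
- **That the entry criterion guarantees a wide range of starting values.** It is mainly a floor. The MRI route may admit lower scores, but the article states neither a maximum nor a spread for the UCSS.
- **That power for PDT once against control would rise from 58% to 76%, 70% or 65%.** Those figures use a difference of 0.80 − 0.33 = 0.47, hence a control mean of −0.33. The printed means differ by 0.33 + 0.80 = 1.13, for which power at 33 per arm already exceeds 99.9%.
- **That the secondary analyses need the same change.** They have their own repeated-measures plan, and no defect in it is shown here.

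**Conclusion.** The point holds as an efficiency improvement, not as an error that invalidates the plan. The protocol fixes an unadjusted primary model while collecting the covariate most likely to sharpen it.

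With equal variances and an assumed rho of 0.3 to 0.7, the adjusted analysis has 15% to 35% less variance. If the baseline SD is only 0.5 to 0.7 of the follow-up SD, the saving is between nil and 15%. The power gain of about 6 to 14 percentage points also rests on a first pilot mean of −0.33. The article prints +0.33, and the document does not show which is meant. Until that sign is reconciled with the stated 99, the power gain should be quoted only with that condition. Under either sign, the case for narrower intervals and for protection against chance imbalance remains.

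**What to change.** In Statistical analysis, replace the one-way ANOVA for the primary outcome with ANCOVA on UCSS, or on its change, with treatment arm and baseline UCSS as terms. The arm contrasts are the same for either choice of outcome. Report adjusted differences of each PDT arm from control with 95% confidence intervals.

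Name the time point in the same sentence, since that section gives none and the abstract lists weeks 8, 24 and 48; week 8 is the one used for the sample size. Settle the wording before unblinding. Separately, reconcile the sign of the first pilot mean with the stated N.

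Cost: one degree of freedom and a change of wording. No extra data, visits or patients are needed, and SPSS fits the model. The sample size need not change.
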